### Participants

Participants will be recruited from seven sites around the world: Toronto, Montreal, and St John’s (Canada); Los Angeles (United States of America); Groningen (Netherlands); Oldenburg (Germany); and Adelaide (Australia). Each site will aim to recruit a total of 30 participants with a simple randomisation using a 1:1 computer generated allocation (15 randomly assigned to group singing, and 15 randomly assigned to the audiobook club), for a total of 210 participants among all the sites. Participants will not be able to change their allocation.

Recruitment will be variable as each site will have access to different databases, networks, and communities. Hence, recruitment flyers will be sent to a range of organisations such as: deaf and hard-of-hearing organisations, aged-care homes/retirement centres, senior centres, veterans organisations; and to databases such as the Toronto Metropolitan University Auditory Participant Pool and the Toronto Metro Senior Participant Pool. To avoid potential participant bias, flyers will advertise that the study is looking for participants to engage in a creative group activity, rather than group singing or an audiobook club, specifically.

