#### Modelling and inferential statistics

Due to the nature of this research design, there are various levels at which the data will likely show high levels of covariance (e.g., participant, group and site level), also known as clusters. Not accounting for this covariance can lead to inaccurate estimates of standard error, leading to inaccurate hypothesis testing (Mass & Cox, 2004). A well-known modeling technique that can account for this is mixed-effects linear modeling (MLM) and is also well suited to handle missing data in case of attrition or outliers (Pinheiro & Bates, 2000). MLM accounts for covariance at various levels using random effects, which allow for variance in the slope, or intercept. These random effects are defined within the model parameters based on the clustering in the research design. For our purposes, we will define a random-intercept for individual participant, to account for covariance in the repeated measures, and a random-slope for group, to account for the group level covariance.

The third level of nesting (i.e., site) is not accounted for in the model because we do not have hypotheses relating to the different sites. Modeling the third level will result in an unnecessary overly complicated model, but ignoring the third level of clustering could result in heteroscedasticity of model residuals, underestimated standard errors and biased *p*-values. To address this, we will plot and visually assess the proposed model’s residuals. If there is heteroscedasticity of the model residuals, we will apply a robust standard error estimator to account for the clustering [124]. All modeling will be done in the *lme4* package [125] in R.

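### The named method, simple randomisation, cannot guarantee the 15/15 split per site given in the same sentence, and site is left out of the model

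*Protocol article*

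**What the plan says.** The Participants section of the protocol article gives method and result together. Each site, with a target of 30 participants, is to use "simple randomisation using a 1:1 computer generated allocation (15 randomly assigned to group singing, and 15 randomly assigned to the audiobook club"). The same section names seven sites and gives the total: "for a total of 210 participants among all the sites". Nothing in the article mentions blocking, stratification by site or a fixed-quota list that would reconcile the method with the split.

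On analysis, Modelling and inferential statistics says that site "is not accounted for in the model because we do not have hypotheses relating to the different sites". The only safeguard is conditional: "If there is heteroscedasticity of the model residuals, we will apply a robust standard error estimator to account for the clustering". The Tests of equivalence section relies on random assignment to balance a list of covariates, and site is not among those named.

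**The concern.** In the usual sense of the term, simple randomisation is an independent 1:1 draw for each participant. Arm size at a site is then a random variable, and 15/15 is its expectation rather than its outcome. A fixed 15/15 needs restricted allocation within each site. A site that follows the named method literally will usually miss the stated split.

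Two things depend on this. First, the interventions are delivered to groups. The article reads as one choir and one club per site, though it does not say so outright, so arm size would be group size. Some outcomes concern the group itself: the Inclusion of Other in the Self scale asks about the assigned group, and heart-rate-variability synchrony is measured between participants in a session. At a 20/10 site, the arms would differ in group size as well as in activity.

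Second, sites differ in language, speech-test sentences and recruitment source. If change over time also differs by site, chance imbalance within sites adds noise to the arm comparison. A robust standard error alters the stated uncertainty but does not adjust the estimated arm difference for site imbalance.

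**Working it through.** **Inputs from the article.** Seven sites, 30 per site, 1:1 allocation, 15/15 stated per site, site not modelled, alpha 0.05.

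**The plan's own totals.** 15 + 15 = 30 per site, and 7 × 30 = 210. These agree.

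**Allocation under simple randomisation.** The singing-arm size at a site of 30 is X ~ Binomial(30, 0.5), with standard deviation √(30 × 0.25) = 2.7. Sites are independent, so for an event of probability q at one site, P(at least one of seven) = 1 − (1 − q)^7.

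| Split at a site | One site | At least one of seven |
|---|---|---|
| 18/12 or worse | 0.362 | 0.957 |
| 19/11 or worse | 0.200 | 0.791 |
| 20/10 or worse | 0.099 | 0.517 |

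- P(exactly 15/15) = C(30,15)/2^30 = 0.144 at one site.
- P(exactly 15/15 at all seven) = 0.1445^7 = 1.3 × 10⁻⁶. The expected number of exact sites is 7 × 0.1445 = 1.0.
- The mean absolute gap between arms at a site is 4.3 participants.

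Under a fixed list of 15 + 15, a site that reaches 30 has 15/15 with certainty.

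**Effect on the arm comparison.** The article gives no site share of variance in change scores, so an intraclass correlation (ICC) of 0 to 0.20 is assumed. Change scores for 7 × 30 participants were simulated with total SD 1, no treatment effect and site ignored in the analysis (6,000 trials per setting).

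| Assumed ICC | SE, simple | SE, 15/15 per site | Type I error, simple | Type I error, 15/15 |
|---|---|---|---|---|
| 0 | 0.139 | 0.139 | 5.3% | 5.5% |
| 0.02 | 0.140 | 0.136 | 5.4% | 4.7% |
| 0.05 | 0.138 | 0.133 | 5.0% | 4.3% |
| 0.10 | 0.138 | 0.131 | 5.0% | 4.3% |
| 0.20 | 0.138 | 0.123 | 5.4% | 3.3% |

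The mean arm difference was about 0 in every setting. Theory agrees at ICC 0.10: the SE is √(4/210) = 0.138 under simple allocation and √(4 × 0.90/210) = 0.131 with 15/15 at each site.

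**What modelling site would recover.** With simple allocation but site in the model, the average of n₁n₀ at a site is 15² − 30 × 0.25 = 217.5, against 225 at exact balance, a ratio of 0.967. At ICC 0.10 the SE becomes about √(4 × 0.90/210/0.967) = 0.133. The model term therefore recovers most of the precision, and the restriction secures the group sizes and the rest.

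**Overall imbalance.** This is immaterial: a 112/98 split keeps (112 × 98/210)/52.5 = 99.6% of the efficiency of 105/105.

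**The case against.** The strongest reply is that *simple* was used loosely. The sentence fixes 15 and 15 for each site, and a natural reading is a computer-generated list of 15 + 15. The imbalance probabilities then do not apply. List-generation detail is also commonly left to a full protocol, and the appendices the article cites are not shown. This stands in part: the text does not settle which scheme is used, and the lack of a blocking statement is not itself the fault. The fault is that the method named conflicts with the result stated. On the loose reading the name is wrong, and allocation is restricted by a factor the model omits, which produces the conservative type I errors in the last column of the simulation table.

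A reader might infer stronger things that the article does not support:

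- **That site biases the arm comparison.** Each participant has the same allocation probability at every site, so arm and site are independent in expectation. Simulated type I error stayed at 5.0 to 5.4% under simple allocation.
- **That all site differences carry through.** The macro test is group by session and micro outcomes are pre-to-post differences, so stable site differences largely cancel. Only site differences in change matter.
- **That leader effects would be cured by balance.** The choir master and the club facilitator are different roles, so leader is tied to arm within a site whatever the split.
- **That a small arm makes a choir or club unworkable.** An arm of 10 falls to 10 × 0.8 = 8 after the article's 20% attrition, but no minimum group size is stated.

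**Conclusion.** The point holds as an inconsistency between method and result with moderate consequences. Read literally, simple randomisation cannot guarantee 15/15. The split arises by chance at about one site in seven and practically never at all seven, and it is about even odds (52%) that some site is 20/10 or worse. These figures assume exactly 30 recruited at each site and independent 1:1 draws.

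The cost is unequal group sizes and chance imbalance, with an SE about 5% larger at an assumed ICC of 0.10 (0.138/0.131 = 1.05). At an ICC of 0.20 it is about 12% larger (0.138/0.123 = 1.12), and at an ICC of 0 there is no loss. The ICC is an assumption throughout. If a fixed list is intended, the imbalance disappears, but the unmodelled restriction makes the test conservative (3.3% at ICC 0.20). Either way the sentence needs correcting and site belongs in the model. The plan's validity is not in doubt on this ground.

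**What to change.** In Participants, replace simple randomisation with computer-generated allocation stratified by site and restricted to 15:15. Either of two forms would do:

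- a random permutation of each site's screened cohort, allocated in one batch, which also keeps the arms equal or within one if a site recruits fewer than 30;
- permuted blocks of concealed, varying size within site.

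In Modelling and inferential statistics, include site as a fixed factor in every model. Macro outcomes need site and site by session, because a site main effect alone would not absorb site differences in change. Micro change scores need site only. The stated reason for omission, having no hypotheses about sites, does not apply to a factor used to restrict allocation.

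The cost is a reworded sentence, a different list setting and a few degrees of freedom (six for site, and six more for site by session). Late allocations become slightly more predictable unless they are batched or the block sizes are concealed. The change should be made before sites randomise, since allocation cannot be redone afterwards.

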#### Inclusion criteria

1) Adults aged 60 years and older; 2) Bilateral mild-to-moderate hearing loss (20–49 dB hearing level, as proposed by the Global Burden of Disease Expert Group [94]), measured using four-frequency pure-tone average across both ears (4FPTA) measured at 500 Hz, 1000 Hz, 2000 Hz, and 4000 Hz; 3) Unaddressed hearing loss (i.e., participants must not currently use a hearing aid, cochlear implant, or assistive listening device); 4) No significant cognitive impairment, to be assessed with the Montreal Cognitive Assessment for people with hearing impairment (MoCA-H) [95], with participants requiring a score ≥ 24; 5) Not use a pacemaker or anti-arrhythmic agents/medications; 6) Not currently participating in regular active music learning (e.g., choir, formal music training) or audiobook clubs within the last year; and 7) Sufficient language capacity to understand and complete the test materials. Note: all materials will be presented written and/or aurally in English at the sites located in Canada, United States of America, and Australia; Dutch at the Netherlands site; and German at the Germany site. Test material examples corresponding to English, Dutch, and German will be provided where applicable.

### Test battery

#### Cognitive screening

MoCA is a validated brief screening tool designed to detect mild cognitive impairment [96]. MoCA-H is an extension of the MoCA, designed specifically for adults with acquired hearing loss [95]. The cognitive domains assessed include short-term memory recall, visuospatial abilities, executive functioning, phonemic fluency, verbal abstraction, attention, concentration, and orientation.

#### Demographics, social networks, musical background, credibility, and expectation

Participants will be asked to provide their demographic details such as age, sex, gender, residential status, and education. We will also measure their social network diversity (e.g., connections with friend, families, neighbours, etc.) with a subscale from the Social Network Index [97]. Participant’s previous musical training will be measured using the Musical Training subscale from the Goldsmith’s Musical Sophistication Index (Gold-MSI) [98]. This 7-item questionnaire captures the participants’ history of formal musical training with more points representing more musical training. Participant perspectives on the credibility and expectations in respect to their assigned group will also be recorded with the credibility/expectancy questionnaire [99].

#### Speech perception materials

The Coordinate Response Matrix (CRM) sentence recognition test will be used to evaluate speech-in-noise (SIN) perception. Our CRM test is based on the original versions that were developed in English by [100–103]. The carrier phrase is a sentence with a call sign of cat or dog and where one of six colors and one of eight numbers are mentioned (e.g., “Show the dog where the green (color) three (number) is.”; “Laat de hond zien waar de groene (color) dire (number)” [Dutch]; “Zeige dem Hund, wo die grüne (color) Drei (number) ist” [German]. We use a two-down/one-down adaptive procedure based on correct color and number identification. Initial step sizes are 10 dB, which is set to 3 dB after two reversals. The test ends after an additional four reversals, generating a speech reception threshold (SRT).

EmoHI is a vocal emotion perception test [104]. The stimuli consist of pseudospeech sentences such as ‘Koun se mina lod belam’ and ‘Nekal ibam soud molen’ that are not meaningful in any Indo-European languages and are based on the Geneva Multimodal Emotion Portrayal (GEMEP) Corpus materials [105]. Stimuli were spoken by four monolingual native Dutch speakers (two male, two female) without any discernible regional accent, consisting of three emotions: happy, angry, and sad. These were selected for the widest applicability across age ranges [106], and for maximum comparability of the EmoHI test across populations of differing hearing profiles [104]. Stimuli were recorded in an anechoic room at a sampling rate of 44.1 kHz and equalized in RMS. The materials and methods of the EmoHI test are the same as in a previous study [104], but the current interface will not have a child-directed game-like environment. Participants will instead be instructed to listen to the pseudo-sentences and determine whether the voice of the speaker sounded happy, sad, or angry, by clicking on one of three corresponding buttons on the screen labeled “blij”/happy, “verdrietig”/sad, “boos”/angry. For practice, three additional stimuli (one per emotion, one production per speaker) will be used for the training session, but not included in the experimental phase. For the experiment, 36 vocal emotion stimuli are used, comprising the categories happy, sad and angry, with 12 items in each category (4 speakers x 3 utterances). Each emotion category comprises both arousal and valence dimensions: either high or low arousal, or positive or negative valence. Practice items, but not experimental items, will be presented with feedback. Experiment items will be presented in randomized order in one block of approximately 6 to 8 minutes.

#### Music perception materials

A Frequency Difference Limen (FDL) task will be used to evaluate pitch perception. Participants will be presented with a three-alternative forced choice (3AFC) paradigm containing two pure tones (200 ms in duration, with 20 ms envelope rise and fall times) at 500 Hz, with the target stimulus adaptively presented at a higher frequency. The participant will identify which corresponding tone is higher on a computer keyboard (i.e., the first, second, or third tone). A pitch discrimination threshold will be calculated with an adaptive staircase procedure with the frequency difference between the target and 500 Hz tones divided by two after three correct responses, or multiplied by two after one incorrect response. After five reversals, the step size will change, with the frequency difference divided by 1.414 after 3 correct responses or multiplied by 1.414 after one incorrect response. Participants will complete two-blocks, with each block ending after 12 reversals. The calculation of their FDL threshold is determined from the mean of the last 10 reversals of each block, which were then averaged between the two blocks.

The Beat Alignment Test (BAT) will be used to measure musical beat perception and rhythm [107]. The BAT consists of 36 musical excerpts that are played with a superimposed click track in three conditions that are: 1) “On beat”—on the beat; 2) “Off beat”—off the beat with the wrong tempo; and 3) “Phase error”—out of phase. Participants will be provided with practice trials. The task is to identify if the excerpt is on the beat by responding on a keyboard with YES or NO. Participants will be instructed not to tap or move along to the music.

The Spectral-temporally Modulated Ripple Test (SMRT) is a measure of spectral resolution [108], which will be used as a proxy measure of timbre perception. Compared to typical spectral resolution tasks, the SMRT features dynamically changing ripples. Participants will be presented with a three-alternative forced choice (3-AFC) task. The target choice is presented at an initial presentation of 0.5 ripples per octave (rpo), while the other two choices are presented at a reference stimuli of 20 ripples rpo. The target stimuli are modified with a 1-up 1-down adaptive procedure with a step size of 0.2 rpo. After 10 reversals, a threshold is derived from the average of the last six reversals.

The Music-in-Noise Task (MINT) will be used to measure inter-individual differences in hearing-in-noise skills [109]. MINT is utilized as a measure of higher-level musical skills. The MINT uses a match-mismatch trial design, whereby participants first listen to a short instrumental excerpt presented in “multi-music” noise, followed by either a matched or scrambled version of the excerpt presented in silence, and are asked to judge whether the two excerpts are the same. The MINT includes five listening conditions, of which we will utilize three (Baseline, Rhythm, and Prediction [reversed order]), which differ according to the presence or absence of different types of contextual cues, which have been shown to be differentially sensitive to musical and linguistic expertise [109]. The Baseline condition provides no additional cues. In the Rhythm condition, the tones of the instrumental excerpts are all the same pitch within each trial. As such, rhythmic variation between matched and mismatched pairs represents a form of rhythmic cueing. In the Prediction condition, the excerpts are presented in silence first, followed by the noise-masked pair. This predictive cueing helps to anticipate incoming information when the excerpt is presented in noise. Each MINT condition includes 20 trials, with four familiarization trials for each condition prior to the start of the main task. Difficulty is also varied by adjusting the signal-to noise ratio (SNR) between the musical excerpt and the background noise, such that musical excerpts will be more or less hidden in the background noise. Conditions will be tested at four different signal-to-noise levels (0, −3, −6, and −9 dB).

#### Psychosocial questionnaires

*Macro-level* q*uestionnaires*. The 12-item short-form survey version 2 (SF-12v2) from the Medical Outcomes Study (MOS) is a widely used health-related quality of life questionnaire that measures eight health concepts: 1) Physical functioning; 2) Role physical; 3) Bodily pain; 4) General health; 5) Vitality; 6) Social functioning; 7) Role emotional; and 8) Mental health; aggregated as a Physical Summary and a Mental Summary [110]. We will utilize the 1-week (acute) recall period. Scores range from 0 to 100, where a zero score indicates the lowest level of health and 100 indicates the highest level of health.

The Hospital Anxiety and Depression Scale (HADS) consists of 14-items designed to measure symptoms of psychological distress in medical patients [111]. HADS consists of two scales, one for anxiety (HADS-A) and depression (HADS-D). It is an efficient screening instrument that is commonly used in clinical contexts to identify and quantify symptoms related to anxiety and depression. While the original version was validated with adults aged 18 to 65 years; HADS has also been validated as an assessment for adults aged 65 to 80 years old [112]. Scoring for each item ranges from 0 to 3, with a higher score corresponding to higher levels of anxiety or depression.

The Collective Self-Esteem Scale (CSES) is a 16-item scale that evaluates individual and collective identities [113]. There are four distinct subscales (hence there is no total scale score) measuring: 1) membership self-esteem; 2) private collective self-esteem; 3) public collective self-esteem; and 4) and importance to identity, on a scale between 1 and 7, with higher scores associated with higher levels of self-esteem. The CSES is widely used with good reliability.

The revised Social Connectedness Scale (SCS-R) consists of 20-items that measures the psychological sense of belonging and interpersonal closeness in social contexts [113]. Reponses are measured on a Likert scale ranging from 1 = strongly disagree to 6 = strongly agree on items that represent both positive and negative aspects of social connectedness.

*Micro-level questionnaires*. The Positive and Negative Affect Schedule (PANAS) is a widely used measure of mood or emotion that consists of 20-items (10 positive and 10 negative affect items) [114]. Participants will be asked to “Indicate to what extent you feel this way right now, that is, at the present moment” on a scale of 1 = very slightly or not at all; 2 = a little; 3 = moderately; 4 = quite a bit; and 5 = extremely; in respect to affective words such as “interested” or “afraid”.

The Inclusion of Other in the Self Scale (IOS) is a single item that measures how close an individual feels with another person or group [115]. The tool contains 7-pairs of circles consisting of the word “Self” in one circle, and the word “Community” in the other circle. Each pair of circles differs in proximity, from 1 = no overlap; 2 = little overlap; 3 = some overlap; 4 = equal overlap; 5 = strong overlap; 6 = very strong overlap; 7 = most overlap. Participants will select the image that best describes their relationship with their randomly assigned group.

The Subjective Units of Discomfort Scale (SUDS) consists of a 0 to 100-point scale measuring self-rated anxiety and discomfort [116]. We will utilize descriptive anchor points at 0 = “no anxiety, calm, relaxed”; 25 = “mild anxiety, alert, able to cope”; 50 = “moderate anxiety, some trouble concentrating”; 75 = “severe anxiety, thoughts of leaving”; and 100 = “very severe anxiety, worst ever experienced”.

